## Methods

### Study design and setting

This is a multi-centre, randomised controlled trial (RCT) study. Figure 1 illustrates the flow diagram of the study from recruitment and screening for eligible participants to post-training outcome assessments. The RCT takes place in Canada and involves three recruiting sites in two provinces (Québec: Montréal, Sherbrooke; Ontario: Ottawa). The study is ongoing and is currently during subject recruitment phase (May 2017 till present).

**Fig. 1 Fig1:**
[figure not shown]
Study design flow diagram

### Participants

Participants will be recruited using several recruitment procedures such as newspaper advertisement, search in medical archives and former patient lists from each site. Potential participants will first be screened over the phone to determine their interest and initial eligibility to participate in the study following a script for early recruitment, after which they will be invited to attend each site, for a screening visit and evaluation. Screening and clinical evaluations will be performed to verify eligibility to participate. At the beginning of the first study visit, written consent will be obtained from each participant and all participants will be informed about the duration and procedure of the study.

#### Inclusion/exclusion criteria

Males and females will be eligible to participate in the study if they meet the following criteria: 1) are aged 18 years and older; 2) have had solely one stroke; 3) be in a chronic stroke phase (> 6 months) and 4) have completed their rehabilitation treatment. Participants will be excluded from the study if any of the following criteria are met: 1) a significant spasticity at the affected upper limb (a score ≥ 3 on the *modified Ashworth scale*) [36]; 2) a significant pain intensity at the affected upper limb (a score ≥ 6/10 on the Visual Analog Pain Scale) [37]; 3) a major sensory deficit (a score ≤ 25/34 on the *Nottingham Sensory Assessment*) [38]; 3) a presence of hemineglect (> 70% of unshaded lines on the same side as the motor deficit on the *Line Cancellation Test*) [39]; 4) an apraxia (a score > 2.5 on the *Alexander Test*) [40]; 5) any cognitive impairments (a score ≤ 2/5 on the *Mini-Cog Test*) [41]; 6) the presence of a neurological disorder other than a stroke; 7) concomitant orthopaedic problems at the affected upper limb and 8) any contraindication to TMS and/or tDCS, such as epilepsy, metallic implants, a cardiac pace-maker or pregnancy, for female subjects.

### Assessment period

Prior to and following the intervention period, participants will complete clinical and neurophysiological evaluations. Each evaluation day will last approximately 1.5 h and both visits will take place in the week before (baseline) and the week after (post-training) the intervention.

#### Randomisation and blinding

According to the amplitude of their TMS-induced MEP responses, three levels of stratification will be used, which are adapted from Milot et al. [22]: 1) no detectable MEPs (< 50 μV); 2) detectable MEPs (50-120 μV) and 3) clearly detectable MEPs (> 120 μV). Within each stratum, participants will be further randomly allocated into two tDCS groups: 1) tDCS real group and 2) tDCS sham group. Participants will be randomly assigned to either the tDCS real group or the tDCS sham group with a 1:1 allocation. Randomisation allocation will be generated by a computer using a blocked randomisation with variable block sizes of 2 and 4. The participants, the evaluators, involved in the clinical and neurophysiological evaluations, the research staff enrolling participants and the data analysts will be blinded to the tDCS group assignment.

#### Clinical evaluation

Baseline participant information including age, gender, time since stroke and location of stroke will be collected at the initial visit of each participant by a blinded evaluator to help characterize the sample. The clinical evaluations will consist of measurement of the range of motion of shoulder flexion, elbow flexion and wrist extension of both upper limbs, the Fugl-Meyer Stroke Assessment-FMA (upper limb section; 66 = normal) [42], the Box and Block Test [43], the Motor Activity Log [44] and measurement of grip strength, measured by the JAMAR® hand dynamometer.

#### Neurophysiological evaluation

The neurophysiological evaluation will be performed by a trained evaluator blinded to the participants’ tDCS group allocation and will consist of assessment of the integrity of the corticospinal tract and cortical reorganization post training through the use of motor evoked potentials (MEPs) elicited by TMS. For TMS testing, participants will be seated in an armchair with both hands resting in pronation. The participant’s skin will be cleaned with alcohol and surface electromyography (EMG) electrodes will be positioned over the first dorsal interosseous (FDI) of both hands and the extensor carpi radialis (ECR) of the affected arm. Using a TMS system (Magstim 200^2^, Magstim Company, Dyfed, UK) and a 70-mm figure-of-eight coil, we will first determine the hotspot and resting motor threshold (rMT, lowest intensity to evoke reliable MEPs ≥50 μV) from the contralesional hemisphere. These coordinates will be used to guide the identification of the optimal location of the ipsilesional primary motor cortex (M1) of the affected hemisphere, when needed. The rMT will then be determined using the Motor Threshold Assessment Tool software (MTAT 2.0; Clinical Researcher, Knoxville, TN, USA). The software allows for fast estimation of motor threshold through the maximum-likelihood strategy based on the PEST (Parameter Estimation by Sequential Testing) algorithm [45]. Next, a series of suprathreshold stimuli (130% rMT, *n* = 10) will be delivered over the hand motor area to elicit MEP in the resting state. We will repeat these procedures for the ipsilesional hemisphere. If no MEPs can be elicited in the affected FDI, the coil will be moved to target the representation of the arm to elicit MEPs in the affected ECR. If peak-to-peak MEP amplitude of the affected ECR does not reach the chosen threshold of 50 μV, even at the maximum output of the stimulator (100%), the participant’s response will be classified as “MEP absent”. After testing in the resting state, corticomotor excitability of the lesioned hemisphere will be tested in the active state. Participants will remain seated in the armchair and will be asked to actively exert a constant force (20% of maximal voluntary effort depending on the participant’s ability to contract) against a pinch dynamometer on the affected side using a lateral key-pinch with the thumb and index finger. During the contraction (duration 5 s), a suprathreshold TMS pulse (130% of rMT) will be delivered at 3 s to elicit a facilitated MEP along with a silent period (SP). The SP refers to the interruption of EMG activity in the target muscle arising from spinal and cortical inhibition (GABA B receptors) resulting from the stimulation [46]. Both facilitated MEPs and SP will be measured 5 times with at least 30 s between trials to allow for recovery.

### Intervention period

All subjects will participate in an outpatient supervised tailored strength training program, which will follow the recommendations of the American Stroke Association (ASA) position on exercise prescription after stroke [47]. Specifically, it will be a 4-week training intervention, performed 3 times per week non-consecutively, with 3 series per exercise of 10 repetitions and a 2-min break in between exercises. The strength training program will be conducted for 1 h in an outpatient rehabilitation setting and supervised by an experienced trainer who will closely monitor the participants’ exercise performance. The training will commence with a 5-min warm-up comprising of active movements of the muscles to be trained. Using free weights, the one-repetition maximum (1RM), which is the maximum amount of weight load an individual can lift for one repetition, will be estimated by the 10RM [48] in order to avoid tendino-muscular injuries and fatigue. The 10RM will be determined for the muscles playing a key role in the functional performance of the upper limb [49, 50]. These muscles are the wrist extensors and the elbow and shoulder flexors. In addition, the grip muscles of the affected hand will be trained with a JAMAR® dynamometer. Participants’ maximal grip force will be determined and used to dose the training of the hand muscles and its progression.

As intensity plays a crucial role in response to training, the intensity of the strength training program will be tailored to each participant’s potential for recovery based on their baseline MEP amplitudes and gradation of the intensity will follow the ASA recommendation [47] and will be based on the 1RM. This same gradation will be applied for the hand muscles based on the participants’ maximal grip force on the JAMAR®. Thus, for participants in the MEP < 50 μV strata (no detectable MEP; low potential for recovery), the training will start at 35% of the 1RM for each muscle group and will then be increased by 10% each week to reach 50% of the 1RM by week 4. For participants in the MEP 50-120 μV strata (detectable MEP; moderate potential for recovery), the training will start at 50% of the 1RM to reach 65% by week 4. For the participants in the MEP ≥120 μV strata (clearly detectable MEP; high potential for recovery), they will train at 70% of the 1RM during week 1 and progress to 80% of the 1RM at week 4. In combination to the % 1RM, the Borg Rating of Perceived Exertion Scale (BRPE), a measure of an individual’s self-perceived physical exertion during exercise, will be used to further control the intensity of exercise within and between MEP strata while taking into account the individual’s residual ability. The Borg Scale can be accurately rated by chronic stroke survivors and is a valid tool for regulating exercise intensity [51, 52]. Thus, for the first three training weeks, participants in each MEP stratum will train at a perceived intensity between 11 and 13/20 (“fairly light”/“somewhat hard”), corresponding to about 66% of an individual’s maximal effort, and progress toward a perceived intensity between 15 and 17/20 (“hard”/“very hard”), corresponding to about 80% of an individual’s maximal effort, at week 4.

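### The weekly load step for the low-MEP stratum does not lead from 35% to the stated 50% of 1RM; a step of 5 percentage points does

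*Protocol article*

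**What the plan says.** The Intervention period section of the protocol article sets training load by MEP stratum.

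- **Low stratum (MEP below 50 μV):** training starts at 35% of 1RM for each muscle group and "will then be increased by 10% each week to reach 50% of the 1RM by week 4". The Abstract (Methods) gives the same range, 35 to 50%.
- **Moderate stratum (50 to 120 μV):** "the training will start at 50% of the 1RM to reach 65% by week 4". No weekly step is given.
- **High stratum (above 120 μV):** "they will train at 70% of the 1RM during week 1 and progress to 80% of the 1RM at week 4". No weekly step is given.

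On duration, the section says "it will be a 4-week training intervention, performed 3 times per week non-consecutively". On grip training it says "This same gradation will be applied for the hand muscles", with maximal grip force in place of 1RM. The Borg scale "will be used to further control the intensity of exercise within and between MEP strata", with a target of 11 to 13 in weeks 1 to 3 and 15 to 17 in week 4, the same for every stratum.

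**The concern.** The low-stratum sentence fixes a start, a weekly step and an end, and the three do not agree. It is a dosing rule for one of three strata, in a trial whose stated primary goal concerns a programme tailored by intensity. The step is also the only thing the article says about the load in weeks 2 and 3.

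A trainer who reads the step as percentage points and follows it through would bring the low stratum to the moderate stratum's end load at week 4, removing the dose separation that the tailoring relies on. A trainer who reads it as a relative increase would stop short of the stated end. Because the same gradation governs the hand muscles, the error carries over to grip training.

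**Working it through.** **Inputs**

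- Low stratum: start 35%, step 10% each week, end 50% at week 4 (Intervention period). The 35 to 50% range is repeated in the Abstract.
- Moderate stratum: 50% to 65%. High stratum: 70% to 80% (Intervention period).
- Programme: 4 weeks, 3 sessions per week, so 12 sessions. With the starting load in week 1, increases fall at weeks 2, 3 and 4, so the number of increases is k = 3. The high-stratum sentence counts from week 1 to week 4 in the same way.

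**Step 1: try to reproduce the stated 50%**

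| Reading of 10% each week | Formula | Weeks 1 to 4 (% of 1RM) | Week 4 minus 50 |
|---|---|---|---|
| Percentage points | 35 + 10k | 35, 45, 55, 65 | +15 |
| Relative, compounding | 35 × 1.10^k | 35, 38.5, 42.35, 46.59 | −3.4 |
| Relative to the starting load | 35 + 3.5k | 35, 38.5, 42, 45.5 | −4.5 |

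None gives 50%. A compounding step that did would be (50/35)^(1/3) − 1 = 12.6% per week.

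**Step 2: allow a fourth increase**

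- Compounding: 35 × 1.10^4 = 51.2%.
- On the starting load: 35 + 4 × 3.5 = 49.0%.
- Percentage points: 35 + 40 = 75%.

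Two of these come close, but none equals 50%, and a fourth increase before or at week 4 does not fit a week-1 start.

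**Step 3: find the step that fits**

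- Low: (50 − 35)/3 = 5 points per week, giving 35, 40, 45, 50%.
- Moderate: (65 − 50)/3 = 5 points per week.
- High: (80 − 70)/3 = 3.3 points per week. So 5 points is not a rule common to all three strata.

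**Step 4: size of the ambiguity among readings that reach 50%**

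- Linear: 35, 40, 45, 50%; mean (35 + 40 + 45 + 50)/4 = 42.5%.
- Ten points per week, stopped at 50%: 35, 45, 50, 50%; mean (35 + 45 + 50 + 50)/4 = 45.0%.
- Differences by week: 0, 5, 5, 0 points. They fall in weeks 2 and 3, which is 2 × 3 = 6 of 12 sessions. The means differ by 2.5 points.

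**Step 5: gap to the moderate stratum under the literal percentage-point reading**

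- Week 1: 50 − 35 = 15. Week 4: 65 − 65 = 0. Both follow from stated loads and the stated step.
- Week 2: 55 − 45 = 10. Week 3: 60 − 55 = 5. These two assume that the moderate stratum rises linearly, which the article does not say.

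**The case against.** The strongest reply is that the destination is clear even if the path is not. The 50% end is in the sentence itself and the range is in the Abstract, so a trainer can raise the load until 50% is reached and then hold it. On that view the 65% figure arises only by ignoring the stated end. Part of this stands: 65% is the result of following the step literally, not the likely practice, and the realistic spread is the 2.5 to 5 points in step 4. But no cap is stated, and 35, 45, 50, 50% rises by 10, then 5, then 0, which is not a 10% rise each week.

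A second reply is that a relative 10% was meant and loosely rounded, since a fourth increase gives 51.2% or 49.0%. This is possible as an account of how the sentence arose. It does not reconcile the figures, because only three increases fit before the end of a 4-week programme that begins at 35%.

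A third reply is that 5 points is a guess at intent: it does not fit the high stratum, and no step is stated for the other two. That is fair, and it is why the clinical team should confirm the correction. It does not make the 10% figure right.

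Finally, training is "supervised by an experienced trainer who will closely monitor" performance, and the Borg targets add a second control. Both limit the consequence. Neither sets the percentage of 1RM, and one Borg band for weeks 1 to 3 cannot tell a trainer whether week 2 should be 38.5, 40 or 45%.

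**Conclusion.** The concern holds and is minor. The start, step and end given for the low stratum cannot all be true. The start and end are each stated twice and the step once, so the step is the figure to correct.

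The size depends on the reading. The end load is 15 points too high if the step is followed as percentage points and 3.4 to 4.5 points too low if it is relative. Among readings that honour 50%, the difference is 5 points in 6 of 12 sessions. All of this rests on three increases, with the starting load used in week 1.

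The article does not show what instructions the trainers at the sites hold, so different progressions between sites are possible but not shown. It gives no dose-response figure, so no effect on the Fugl-Meyer score is claimed. The Randomisation and blinding section says "Within each stratum, participants will be further randomly allocated into two tDCS groups", so the real-versus-sham comparison, the sample size and the planned analysis are untouched.

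**What to change.** Replace the 10% weekly increase for the low stratum with 5 percentage points per week, and write out the loads: 35, 40, 45 and 50% of 1RM in weeks 1 to 4, with the same percentages of maximal grip force for the hand muscles. The clinical team should confirm that this is the intended progression before the text is changed.

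The cost is a one-line correction and a note to the three sites. The article describes recruitment as ongoing, so each site can report in the same exchange which progression it has used in this stratum so far.

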#### Transcranial direct current stimulation (tDCS)

An anodal montage over the ipsilesional hemisphere will be used. The localisation of the lesioned M1 and placement of electrodes will follow the protocol from DaSilva et al. [53]. In essence, the vertex will be located by marking the distance halfway between the nasion and inion and the distance between the right/left pre-auricular points. Location of M1, corresponding to C3/C4 on the EEG system, will be estimated by using 20% of the pre-auricular distance from the vertex. The anode will be placed over the M1 area whereas the cathode will be placed on the contralateral supra-orbital region. For the tDCS group, a direct current will be generated by a tDCS stimulator and gradually increased in a ramp-like fashion over the first 8 s until a maximum intensity of 2 mA is achieved. The tDCS will be applied for 20 min during each training session for a total of 12 sessions. The parameters chosen in the proposed project are considered safe for the application of tDCS [30, 31, 54]. For the group receiving sham tDCS, the protocol will be similar to the tDCS real group although the stimulation will be applied for the first 30 s only; a duration long enough to induce similar perceived sensation as real tDCS, to ensure blindness of the participants to the tDCS type [55]. After each training session, using a home-developed questionnaire, participants will be questioned about the presence of tDCS symptoms, their intensity and relatedness to tDCS.

If any participants develop contra-indications to the training intervention or the tDCS stimulation, they will be discontinued from the intervention but will be included in an intention to treat analysis.

### Outcome measures

#### Primary outcome measures

The primary outcome measures will be change in Fugl-Meyer Stroke Assessment Scale-FMA (66 = normal) [42], which will be used to assess changes in the trained arm motor function and change in peak-to-peak MEP amplitude, motor threshold and silent period, elicited by TMS, to assess changes in motor cortex excitability and cortical reorganization.

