### Sample size and power calculations

A priori power analysis was performed in G*Power 3.1.9.2, using a two-tailed independent samples t-test having an alpha level of 0.05, to calculate the sample size required in this study. By stratifying participants based on their MEP amplitude to provide an appropriate dosage of training, we expect all participants within the three MEP strata to benefit from the 4-week tailored strength training program. The sample size was thus calculated based on the expected difference in motor function gains between the tDCS real and the tDCS sham groups. Based on the results of studies having used repetitive application of tDCS in chronic stroke survivors, we expect an 8-point gain in FMA for the tDCS real group [56]. Furthermore, preliminary results based on this study showed a 7-point gain on the FMA scale after 4 weeks of strength training for participants presenting pre-training MEPs. Therefore, we estimate that the tDCS sham group (including participants with and without MEP) will show at least a 6-point gain on the FMA scale, exceeding the 5-point gain minimal detectable change (MDC) of this scale [57]. Thus, with an estimated average difference in FMA gain between both groups of 2 points (SD = 3), with an effect size of 0.66 and a power of 85%, we calculated that a total of 84 participants will be needed to detect differences between groups. However, presuming an attrition rate of 20%, a total of 105 participants will be recruited for the purpose of this study.

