### Statistical analysis

Descriptive statistics will be used to characterize the sample. We will verify if, at the beginning, the two tDCS groups will be comparable by using independent t-tests or Chi-squared tests, depending on the nature of the variables. To evaluate the impact of tailored exercises based on MEP stratification on changes in FMA and MEP measures, as well as the impact of tDCS on enhancement of training response, a two-way 3X2 ANOVA [MEP strata (three levels) and type of tDCS (2 levels)] will be used. The significance level will be set at 0.05. If an interaction is noted, paired *t*-tests will be used to locate any significant differences in each stratum with a Bonferroni correction for multiple tests (adjusted *p*-value of 0.02).

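### Four outcomes are called primary with no alpha shared among them, yet the trial is sized on FMA alone; if any one can count, the tDCS false-positive chance is up to about 18.5%

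*Protocol article*

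**What the plan says.** Three sections of the protocol article bear on this point.

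- **Primary outcome measures.** The section opens "The primary outcome measures will be change in Fugl-Meyer Stroke Assessment Scale-FMA (66 = normal" and carries on in the same sentence with "change in peak-to-peak MEP amplitude, motor threshold and silent period, elicited by TMS, to assess changes in motor cortex excitability". Four changes are therefore primary: FMA, MEP amplitude, motor threshold and silent period. None is ranked above another, and nothing says whether one or all must be significant.
- **Statistical analysis.** The analysis is meant to evaluate "changes in FMA and MEP measures, as well as the impact of tDCS on enhancement of training response", and for this "a two-way 3X2 ANOVA [MEP strata (three levels) and type of tDCS (2 levels)] will be used". Then: "The significance level will be set at 0.05". The one correction named is for follow-up tests after an interaction, "to locate any significant differences in each stratum with a Bonferroni correction for multiple tests".
- **Sample size and power calculations.** "The sample size was thus calculated based on the expected difference in motor function gains between the tDCS real and the tDCS sham groups". The calculation was done "using a two-tailed independent samples t-test having an alpha level of 0.05". No power is given for any TMS outcome.

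The last paragraph of the Background is also relevant. It frames both the primary goal (tailored strength training) and the secondary aim (adding tDCS) in terms of arm function.

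**The concern.** When several outcomes share primary status and each is tested at 0.05, the 5% applies to each test and not to the trial's conclusion. Without a ranking, a success rule or a split of alpha, a significant tDCS effect on any of the four could be reported as a positive primary result.

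The sample size points the other way. It treats the FMA comparison as the only one that matters and spends the full 0.05 on it. The four primaries, the single 0.05 and the 84 participants therefore do not fit together. Either FMA alone is confirmatory, or alpha has to be shared and the trial is too small for its stated power.

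**Working it through.** **Inputs.** From the Sample size section: a difference of 2 FMA points, SD 3, effect size 0.66, two-sided alpha 0.05, power 85%, N = 84, and 105 after 20% attrition. From Randomisation and blinding: 1:1 allocation to real or sham tDCS within three MEP strata. From Primary outcome measures: four outcomes. From Statistical analysis: alpha 0.05, not divided across outcomes. The document gives no correlations between outcomes, so those below are assumptions.

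**1. The plan's own figure.** The standardised difference is 2/3 = 0.667. A two-sided two-sample t-test (noncentral t) with 85% power needs 41.4, so 42 per arm and 84 in total. Power at 42 per arm is 85.5%, or 84.8% with the rounded 0.66. Attrition: 84/0.8 = 105. The stated numbers reproduce, for FMA alone at the full 0.05.

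**2. One tDCS test per primary outcome, any one counting.**

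- Four independent outcomes: 1 − 0.95^4 = 0.185, or 18.5%. The Bonferroni bound is 4 × 0.05 = 20%, so 18.5% is close to the ceiling.
- FMA and MEP amplitude only: 1 − 0.95^2 = 0.0975, or 9.75% (bound 10%).

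**3. Correlated outcomes.** The 3×2 ANOVA was simulated with no true effects, 14 per cell (6 × 14 = 84; equal cells are an assumption), four outcomes with a common correlation, and 60,000 runs per row. The chance of at least one significant tDCS main effect was:

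| Assumed correlation | At least one false positive |
|---|---|
| 0 | 18.6% |
| 0.3 | 17.5% |
| 0.5 | 15.5% |
| 0.7 | 13.3% |
| 0.9 | 9.6% |

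The 18.6% in the first row agrees with the exact 18.5% within simulation error.

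**4. What keeping four primaries would cost.** Bonferroni over four gives 0.05/4 = 0.0125 per outcome, and the overall error is 1 − 0.9875^4 = 4.9%. The FMA comparison at 85% power then needs 57.8, so 58 per arm and 116 in total, or 116/0.8 = 145 with attrition. With an effect size of 0.66 it is 59 per arm, 118 in total and 148 with attrition. At the planned 84, FMA power falls to about 69% (68% with 0.66).

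**The case against.** The strongest reply is that the document already leans towards FMA. Both aims concern arm function, the Primary outcome measures section assigns arm function to FMA and cortical excitability to the TMS measures, and the sample size uses FMA only. A positive silent-period result could not support an arm-function conclusion, and nowhere does the text say that any one of the four suffices. Ranking of outcomes is also often left to the SAP, which is not shown.

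Part of this stands. The any-of-four rule is a reading and not a quotation. If all four had to be significant, there would be no inflation. But the text does state four outcomes as primary, does state 0.05, and does address multiplicity, only in a different place. That is a flaw in what is fixed here and not a detail left for later.

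Two further limits also stand. The Statistical analysis section speaks of MEP measures without naming threshold or silent period. If amplitude alone is meant, the figure drops to at most about 10%, and two declared primaries have no stated test. And 18.5% should not be read as a floor for the tDCS effect, because correlated outcomes lower it. Three of the four come from the same TMS evaluation, so independence is not a safe assumption.

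A reader might also count every F-test in the ANOVA and quote 1 − 0.95^8 = 33.7% or 1 − 0.95^12 = 46.0%. The document does not support these as the chance of a false primary success. The MEP strata are not randomised and train at different intensities by design. All three are expected to benefit, so a difference between strata is not the hoped-for result. An interaction leads to stratum tests that carry their own correction. The error rate would rise above the figures for tDCS alone only if those effects were also presented as primary evidence.

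**Conclusion.** The point holds in this form. Four outcomes are declared primary, alpha is not shared among them, and only FMA is powered, so the nominal 5% does not hold across the declared primaries if any one of them counts.

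For the randomised tDCS contrast the false-positive chance is up to about 18.5%, roughly 10 to 18% under assumed common correlations of 0.9 down to 0, and at most about 10% if only FMA and MEP amplitude are tested. These figures assume an any-one-counts rule, which the text neither states nor excludes. The FMA sample size itself is sound.

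**What to change.** - Name change in FMA as the single primary outcome, and real versus sham tDCS as the single confirmatory test at 0.05. It is the only contrast that is both randomised and powered.
- Move MEP amplitude, motor threshold and silent period to secondary mechanistic outcomes, reported with confidence intervals and no confirmatory claim. Name each one in the Statistical analysis section, so that its analysis is clear.
- State that the stratum effect and the interaction are supportive.
- Align the aims. The Background makes the tailored training programme the primary goal and the tDCS comparison secondary, so this fix reverses their order. The amendment should say so openly.

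**Cost.** N = 84 (105 recruited) and the stated 85% power for FMA are unchanged, and no data collection changes. The TMS measures lose primary status, and the stated aims and the registry entry must be amended. The article reports that recruitment is ongoing and that analysts are blinded to tDCS assignment. The amendment should be dated before unblinding.
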